### Sample size

To calculate the number of participants, we focus on the primary endpoints of ‘moderate to vigorous PA (min/week)’ and ‘PAHCO’, including cluster adjustment. As the primary outcomes lead to four statistical tests, a Bonferroni correction is used accordingly with *α *= 0.05/4. With an assumed drop-out rate of 10%, a sample size of 567 participants from 24 medical practices (α = 0.0125, power = 80%) is required to detect differences between both intervention groups of low to moderate effect size (*f* = 0.175). To account for the effects of clustering, an intraclass correlation (ICC) of 0.02 is considered, estimated based on previous studies for cRCTs in primary care [26, 27]. We consider this ICC to be realistic in our trial as the participating practices are similarly structured (professional background, qualification level, treating patient group size and region) and were trained by the research team.

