### Randomisation, allocation and blinding

A cRCT with randomisation at the physician practice level will be conducted for organisational reasons and to avoid the risk of mixing participants from both groups within a medical facility (contamination). The research team will recruit the physicians and provide them with detailed information about the study or answer questions. After physicians express interest in participating in the study and meet the inclusion criteria, they must provide written informed consent, which needs to be supported by the cooperating health insurance company. Each medical practice will be randomly allocated to the PARS or PAA group using computer-based block randomisation (Excel 2016). Due to the local density of physician practices in the Nürnberg metropolitan region, six blocks for randomisation will be defined (Nürnberg city [*n* = 10], Nürnberg surrounding area [*n* = 2], Fürth city [*n* = 10], Fürth surrounding area [*n* = 2], Erlangen city [*n* = 10] and Erlangen surrounding area [*n* = 2]). The practices will then be informed about further procedures, and physicians, as well as medical staff working in the facility, will undergo specific training according to the assigned intervention arms.

Because of group-specific procedures and the corresponding training, blinding the participating actors (physicians, exercise professionals) is not possible in this study. However, blinding participants is possible due to randomisation on the physician practices’ level. The participants will only be informed about the intervention in which they are involved and will not come into contact with the other intervention arm during the study. The statistician will also be blinded to the group allocation until completion of the statistical analysis.

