### Data analysis

A linear modelling approach will be used to analyse the effectiveness of the intervention. The group information (PARS vs PAA) will constitute the decisive independent variable to be modelled on participants’ outcomes after the intervention. In this context, participants’ baseline values will be integrated into the calculations to control for potential differences before the intervention. Given the clustered design, it is necessary to account for the nested character of the data (level 2: physicians; level 1: patients). Depending on the final number of clusters included (level 2), participants recruited (level 1) and the power achieved, either physicians will be included as a control variable or the hierarchical structure will be considered through multilevel structural equation modelling (applying the Kenward-Roger correction for small cluster sizes [45]).

Adopting an intention-to-treat paradigm, we will include all participants who have been randomised in the analysis. To avoid underestimation of treatment effects through conservative replacement strategies (such as baseline observation carried forward), we will apply imputation techniques to this trial. Accordingly, dropouts and missing data will be treated by applying full information maximum likelihood (FIML) imputation. The Mardia test, with its inspection of statistical skewness and kurtosis, will determine multivariate normality. If the assumptions of normality are violated, the calculations will be based on robust maximum likelihood (MLR) procedures.

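### The stated 80% power follows from its own inputs only if the between-practice degrees of freedom are ignored; with about 22 they give about 73% before any gain from baseline adjustment

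*Protocol article*

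**What the plan says.** The Sample size section of the protocol article ties the power to a specific design: "a sample size of 567 participants from 24 medical practices (α = 0.0125, power = 80%) is required to detect differences" between the arms, described as of "low to moderate effect size" (f = 0.175). The alpha is 0.05/4 by Bonferroni. On attrition it says "With an assumed drop-out rate of 10"%, and on clustering "an intraclass correlation (ICC) of 0.02 is considered". The section names no degrees of freedom, no variation in practice size and no correlation between baseline and outcome.

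The Randomisation section makes the practice the unit of allocation: "Each medical practice will be randomly allocated to the PARS or PAA group using computer-based block randomisation (Excel 2016").

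The Data analysis section says that baseline values enter the model. It leaves two ways to handle clustering, to be chosen once the numbers of clusters and participants and the achieved power are known. One enters physicians as a control variable. The other is a multilevel structural equation model, "applying the Kenward-Roger correction for small cluster sizes".

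**The concern.** When whole practices are randomised, the arm effect is a contrast between practices. Its precision is estimated from 24 practice-level units, so a valid test refers to a t distribution with about 22 degrees of freedom, however many patients each practice recruits. At an alpha as small as 0.0125 the difference from the normal distribution is not trivial. The sample size section allows for the ICC through variance inflation but seems to make no allowance for the small number of practices, whereas one branch of the analysis section does. The two sections then rest on different reference distributions.

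At stake is how the primary tests are read. If the true power is nearer 73%, the type II error is about 27% rather than 20%, and a null result would look better powered than it is.

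**Working it through.** **Inputs from the Sample size section.** 567 recruited, 10% drop-out, 24 practices, ICC 0.02, f = 0.175, alpha 0.0125.

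**Assumptions.** Two-sided tests (sidedness is not stated, but an effect size f goes with an F test); 12 practices per arm (no ratio is stated); equal practice sizes at first.

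**1. Common quantities**
- Analysed: N = 567 × 0.9 = 510.3
- Mean practice size: m = 510.3 / 24 = 21.26
- Design effect: 1 + (21.26 − 1) × 0.02 = 1.405
- Effective N: 510.3 / 1.405 = 363
- Standardised difference for two equal groups: d = 2f = 0.35
- Noncentrality: d × √(effective N / 4) = 0.35 × √90.8 = 3.335

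**2. Reproducing the stated 80%**
- Normal reference, critical value 2.498: Φ(3.335 − 2.498) = 79.9%
- t reference with 508 individual-level df, critical value 2.507: 79.6%

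Working forwards gives much the same. About 366 participants are needed without clustering. Inflating for a fixed 24 practices gives 366 × 0.98 / (1 − 366 × 0.02 / 24) = 516 analysed, and 516 / 0.9 = 573 recruited, close to 567.

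**3. Same inputs with between-practice degrees of freedom**
- df = 24 − 2 = 22; critical value 2.720
- Noncentral t with noncentrality 3.335: power = 72.5%
- A simulation of 24 practices of 21 patients with a 22-df cluster-level test gave 72.1%

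**4. Detectable effect**
- With 22 df, 80% power needs a noncentrality of 3.598
- f = 0.175 × 3.598 / 3.335 = 0.189

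**5. Unequal practice sizes.** Design effect 1 + ((1 + CV²) × m − 1) × 0.02. The article gives no coefficient of variation (CV), so the values are assumed.

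| CV | Design effect | Power, 22 df |
|---|---|---|
| 0 | 1.405 | 72.5% |
| 0.3 | 1.444 | 71% |
| 0.5 | 1.512 | 69% |
| 0.65 | 1.585 | 66% |

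A likelihood-based mixed model uses unequal practices somewhat more efficiently; an approximation for that case gives 72%, 70% and 68% for the last three rows.

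**6. Baseline adjustment.** If f is on the unadjusted scale and the variance falls by the factor 1 − r², the noncentrality becomes 3.335 / √(1 − r²). With equal practice sizes and 22 df:

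| r | Power |
|---|---|
| 0 | 72.5% |
| 0.3 | 77% |
| 0.38 | 80% |
| 0.5 | 86% |
| 0.6 | 91% |

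If f is already on the adjusted scale, there is no such gain.

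**7. Number of practices.** The block sizes in the Randomisation section add to 10 + 2 + 10 + 2 + 10 + 2 = 36, not 24. With 510.3 analysed in 36 practices, m = 14.18, the design effect is 1.264, df = 34, and power is 80.4%.

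**The case against.** The strongest reply is that 72.5% charges the plan for the degrees of freedom and gives no credit for baseline adjustment, although both come from the same analysis section. That stands. A reader might infer that the trial as analysed will have only 73% power. The documents do not support this: they give no baseline-outcome correlation and do not say on which scale f is expressed, so power under the full analysis could be above or below 80%. What does not stand is using this to defend the stated figure, because the sample size inputs already reach 79.9% without any correlation.

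A second reply is that Kenward-Roger is only one of two conditional branches. This is true, and it would be too strong to say that the plan is committed to it. But the 22 degrees of freedom come from randomising practices, not from the choice of correction. Entering physicians as a control variable is no valid way round: with allocation by practice, physician or practice fixed effects are aliased with arm.

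Third, it would be wrong to say that 80% arises only from a normal approximation. Any method that ignores the practice-level degrees of freedom gives about that figure. With 22 degrees of freedom and an ICC of 0.01, power would be 80.2% (and 53.6% at an ICC of 0.05), but the stated ICC is 0.02. A one-sided test at 0.0125 with 22 degrees of freedom would give 81.6%, but it would need only about 537 recruited, which does not match 567.

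Fourth, the article describes the practices as similar in the size of the patient group treated. That bears on the CV range, which is assumed throughout, and does not guarantee equal recruitment. The 72.5% assumes equal sizes and does not depend on that range.

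Finally, the article condenses a fuller protocol, and the authors' exact method is inferred from a close reproduction. That is a reason to ask for the calculation to be stated, not to accept a figure that its printed inputs do not give.

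**Conclusion.** The point holds as a statement about the sample size calculation as printed. Its inputs give about 80% when the practice-level degrees of freedom are ignored and about 72.5% with 22, a shortfall of about 7 percentage points; the detectable f at 80% power is about 0.189. This rests on two-sided tests, 12 equal-sized practices per arm, and no gain from baseline adjustment. Unequal practice sizes lower the figure by roughly a further 1 to 6 points over the assumed CV range.

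The point does not establish that the full planned analysis is underpowered. A baseline-outcome correlation of about 0.38 or more, with f on the unadjusted scale, would restore 80% at equal practice sizes; roughly 0.40 to 0.49 would be needed over the assumed CV range. The consequence is moderate and the correction is cheap, so it should be made.

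**What to change.** Keep 567 participants and restate the power with a t reference on the number of practices minus 2 degrees of freedom, in one of two forms:

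- about 73% per test at f = 0.175 for 24 equal practices without baseline adjustment, with a range for unequal practice sizes; or
- the baseline-adjusted (ANCOVA) power, with the assumed baseline-outcome correlation and the scale of f both stated.

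The second form is the more informative, because it matches the planned analysis. Base either one on the number of practices actually intended: the abstract and the Sample size section say 24, the randomisation blocks add to 36, and these must be reconciled. Recalculate if the final number of practices differs.

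The cost is a reworded sample size paragraph and one recalculation, with no extra patients. Under the first form the published power becomes less favourable. For comparison, reaching 80% with 22 degrees of freedom and no baseline gain would take about 640 analysed (about 711 recruited) in 24 practices, or about 28 practices of the same size.

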### Randomisation, allocation and blinding

A cRCT with randomisation at the physician practice level will be conducted for organisational reasons and to avoid the risk of mixing participants from both groups within a medical facility (contamination). The research team will recruit the physicians and provide them with detailed information about the study or answer questions. After physicians express interest in participating in the study and meet the inclusion criteria, they must provide written informed consent, which needs to be supported by the cooperating health insurance company. Each medical practice will be randomly allocated to the PARS or PAA group using computer-based block randomisation (Excel 2016). Due to the local density of physician practices in the Nürnberg metropolitan region, six blocks for randomisation will be defined (Nürnberg city [*n* = 10], Nürnberg surrounding area [*n* = 2], Fürth city [*n* = 10], Fürth surrounding area [*n* = 2], Erlangen city [*n* = 10] and Erlangen surrounding area [*n* = 2]). The practices will then be informed about further procedures, and physicians, as well as medical staff working in the facility, will undergo specific training according to the assigned intervention arms.

Because of group-specific procedures and the corresponding training, blinding the participating actors (physicians, exercise professionals) is not possible in this study. However, blinding participants is possible due to randomisation on the physician practices’ level. The participants will only be informed about the intervention in which they are involved and will not come into contact with the other intervention arm during the study. The statistician will also be blinded to the group allocation until completion of the statistical analysis.

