**Methods:**

To evaluate the effectiveness and implementation success of the PARS, we will apply a pragmatic cluster-randomised controlled trial (cRCT) in Hybrid II design by comparing two intervention groups (PARS vs PA advice [PAA]). The trial will take place in the Nürnberg metropolitan region, with 24 physician practices recruiting 567 people with NCDs. Both groups will receive brief PA advice from a physician to initially increase the participants’ motivation to change their activity level. Subsequently, the PARS group will be given individualised support from an exercise professional to increase their PA levels and be transferred to local exercise opportunities. In contrast, participants in the PAA group will receive only the brief PA advice as well as information and an overview of regional PA offerings to become more active at their own initiative. After 12 and 24 weeks, changes in moderate to vigorous PA and in physical activity-related health competence (movement competence, control competence, self-regulation competence) will be measured as primary outcomes. Secondary outcomes will include changes in quality of life. To measure implementation success, we refer to the RE-AIM framework and draw on patient documentation, interviews, focus groups and surveys of the participating actors (physicians, exercise professionals).

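### The randomisation blocks add up to 36 practices while the trial is sized on 24; the difference is unexplained, and 24 practices cannot fill the blocks as listed

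*Protocol article*

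**What the plan says.** The Sample size section requires "a sample size of 567 participants from 24 medical practices", at alpha 0.0125, 80% power, f = 0.175, an ICC of 0.02 and 10% drop-out. The abstract repeats the count: "with 24 physician practices recruiting 567 people with NCDs".

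Under Randomisation, allocation and blinding, each practice is to be "randomly allocated to the PARS or PAA group using computer-based block randomisation (Excel 2016"). There "six blocks for randomisation will be defined", because of the local density of practices: Nürnberg, Fürth and Erlangen city with 10 each, and the area surrounding each city with 2. The section does not give the allocation ratio. It does not say whether practices are allocated one by one or together, or whether the bracketed figures are targets or upper limits. The article mentions no over-recruitment, reserve slots or expected loss of practices.

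The Data analysis section names study arm, the physician level and baseline adjustment ("baseline values will be integrated into the calculations to control for potential differences before the intervention"). It does not mention the randomisation area.

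**The concern.** The number of clusters largely sets the power of a cluster trial, and the article gives two figures for it, 24 and 36. The reader cannot tell whether the block list is out of date, whether it is an allowance for extra practices, or whether the design grew without the calculation being updated.

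The mismatch also affects the allocation itself. A block of 10 guarantees a 5:5 split only when it is full. If 24 practices enter a list built for 36, some blocks stay short or empty, and neither the overall split nor the split within each area is then protected. With so few clusters, a difference of a few practices between the arms is visible.

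**Working it through.** **Inputs from the article.** 24 practices; 567 participants; alpha 0.0125; power 80%; f = 0.175; ICC 0.02; drop-out 10%; block sizes 10, 2, 10, 2, 10, 2.

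**Assumptions.** Two-sided test, 1:1 allocation within blocks, d = 2f = 0.35, equal practice sizes.

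**1. Block total.** 10 + 2 + 10 + 2 + 10 + 2 = 36, which is 12 more than 24.

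**2. Reproducing 567.**
- Without clustering: n per arm = 2(z₁ + z₂)²/d², with z₁ and z₂ the normal quantiles for alpha and power. This gives 183 per arm, 366 in total (368 by the exact F test).
- Analysed participants: 567 × 0.9 = 510.3. Design effect = 1 + (m − 1) × 0.02, with m the number analysed per practice.

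| Practices | m | Design effect | 366 × design effect | ÷ 0.9 | × 1.1 |
|---|---|---|---|---|---|
| 24 | 21.26 | 1.405 | 514.3 | 572 | 566 |
| 36 | 14.18 | 1.264 | 462.4 | 514 | 509 |

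The stated 567 therefore belongs to 24 practices. Taking m before drop-out (567/24) gives 585 to 591 and fits less well. The same variant at 36 gives 522 to 527, still short of 567.

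**3. Can 24 practices fill the blocks exactly?** Blocks that are all either full or empty need 10a + 2b = 24 with a and b at most 3. The only solution is a = 2, b = 2. Exact balance is thus guaranteed only if one city and one surrounding area contribute no practice at all.

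**4. Balance under one plausible filling (assumed): 6 of 10 in each city, all three pairs complete.** Within a city the number in one arm is hypergeometric, with counts out of 210:
- 3:3 has 100/210 = 47.6%, so 4:2 or worse has 52.4%.
- 5:1 or 1:5 has 10/210 = 4.8%. In at least one of three cities: 1 − (200/210)³ = 13.6%.
- Combining the three cities (210³ = 9,261,000 outcomes), exactly 12:12 has 2,590,000/9,261,000 = 28.0%. A split of 13:11 either way has 4,065,000, which leaves 2,606,000/9,261,000 = 28.1% for 14:10 or worse.

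If the 24 practices instead fall at random into the 36 slots, simulation gives 27% and 29%. Simple randomisation of 24 practices gives 16% and 54%.

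**5. Effect on power.** Power = Φ(d/√(DE(1/n₁ + 1/n₂)) − z₁), with DE = 1.405 and 21.26 analysed per practice (normal approximation):

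| Split | 12:12 | 11:13 | 10:14 | 9:15 |
|---|---|---|---|---|
| Power | 79.9% | 79.5% | 78.5% | 76.8% |

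With 36 practices sharing the same 567 participants, power would be 84.6%.

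**The case against.** The bracketed figures may be ceilings per area; the reference to local practice density fits that reading. If so, there is an unexplained number but no error in the design. The sample size itself reproduces at 24, and a larger count would only raise power. This stands in part: the sizing is not in doubt, but the article does not call the figures ceilings, and under that reading the blocks still go part-filled.

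A reader might infer that balance is certainly lost. The documents do not support that. It depends on how practices fill the blocks, which is not stated; one filling keeps 12:12 exactly, and the fillings examined with part-filled blocks are better balanced than simple randomisation.

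A reader might also infer that the analysis ignores area. All that can be said is that this condensed article does not mention it. A covariate list may stand in an analysis plan that is not shown, and leaving out a stratum usually makes inference conservative rather than biased.

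Finally, the second allocation in a pair can be deduced once the first is known, and the research team recruits the practices. This matters only if allocation is sequential, which the article does not say, and in the pairs it concerns at most three practices.

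**Conclusion.** The inconsistency is exact: 36 block places against 24 practices, with no explanation. The participant number rests on 24, so the block plan is out of line with the calculation, unless the design changed and the calculation was not redone.

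Balance by arm and by area is no longer guaranteed. Under the assumed 6-of-10 filling, about 28% of draws give 12:12 and about 28% give 14:10 or worse. The cost in power is small, about 1.4 percentage points at 10:14.

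The mismatch should not be read as showing an underpowered trial: if 36 were meant, 567 would be more than needed under the stated assumptions. The balance figures depend on the assumed filling and on 1:1 allocation within blocks. The power figures depend on d = 2f, a two-sided test, equal practice sizes and the normal approximation.

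**What to change.** - State one number of practices in the abstract, the Sample size section and the randomisation section. Make the block sizes sum to it, or say that they are ceilings and how they will be filled.
- If 36 is meant, restate the sample size calculation with that number.
- For practices not yet randomised (the article gives the trial status as recruiting), allocate each area's consented practices in one batch. Where that is impracticable, use smaller concealed blocks of varying size in the larger areas. An area with only two practices is better handled as one batch: a block of 4 would be half-filled there, and sequential allocation in a block of 2 reveals the second practice's arm.
- Say that the primary model includes the randomisation area, for example city (three levels) and city versus surrounding area (two levels) as fixed effects.

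The cost is a new allocation list for the remaining practices and some wording. The area terms use 2 + 1 = 3 of the 24 − 2 = 22 cluster-level degrees of freedom, which moves the two-sided critical value at alpha 0.0125 from about 2.72 to about 2.76. These additive terms summarise the six areas; a full six-level factor would use 5.

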#### Participants

Suitable patients from the cooperating health insurance companies will be included in the study as part of their routine care (pragmatic trial). Eligible patients will be identified by the physicians or medical staff in advance (see inclusion and exclusion criteria above). Selected patients will receive information about the study and a screening assessment at their routine appointment (see Fig. 2), which will ask about their PA levels and contraindications. After a brief conversation about the benefits of PA with the physician, the patient can decide whether to participate in the programme and is referred to the next level of each intervention arm.

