#### Physical activity referral scheme (PARS)

The PARS pathway is based on a conventional prescription for physical therapy in Germany and includes key actors, such as physicians, exercise professionals and exercise organisations. A detailed description of the pathway according to the PARS reporting checklist by Hanson et al. [28] can be found in Additional file 1.

The referral scheme begins with the physician’s screening. During a routine medical visit, the patient’s eligibility for participation in the study will be assessed. For this purpose, in addition to the inclusion and exclusion criteria described earlier, a short screening questionnaire will be used to determine average weekly PA. The questionnaire is based on three validated questionnaires for evaluating activity levels subjectively (Single-item [29], Physical Activity Vital Sign (PAVS) [30], Kaiser Permanente Southern California Exercise Vital Sign [31]) and is adapted to the trial setting. If the questionnaire reveals suitability – that is, the patient is inactive (< 150 min/week of moderate to vigorous PA) – brief PA advice (10 min) follows. The main goal is to initially motivate patients to change their behaviour and participate in the following intervention. The referral form can then be used to transfer the patient to a participating exercise professional.

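### Patients are identified and invited after allocation by unblinded staff trained for their arm, so who is approached and who accepts can differ between arms; the planned safeguards reduce this but do not remove it

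*Protocol article*

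**What the plan says.** The order of events is set out in two sections of the protocol article.

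- **Allocation comes first.** Under Randomisation, allocation and blinding: "Each medical practice will be randomly allocated to the PARS or PAA group using computer-based block randomisation". Practices are then told how to proceed, and "physicians, as well as medical staff working in the facility, will undergo specific training according to the assigned intervention arms". The same section concedes that "blinding the participating actors (physicians, exercise professionals) is not possible in this study".
- **Patients come afterwards.** Under Recruitment procedures, Participants: "Eligible patients will be identified by the physicians or medical staff in advance". At the routine appointment they receive study information and a screening assessment. Then: "After a brief conversation about the benefits of PA with the physician, the patient can decide whether to participate in the programme".
- **What patients know.** "The participants will only be informed about the intervention in which they are involved" (Randomisation, allocation and blinding). For PARS, the purpose of the physician's advice is described as follows: "The main goal is to initially motivate patients to change their behaviour and participate in the following intervention".
- **What differs.** PARS leads to an initial assessment and six 60-minute sessions with an exercise professional. PAA leads to a brochure.
- **Analysis.** Under Data analysis, participants' "baseline values will be integrated into the calculations to control for potential differences before the intervention". The article names no other patient-level covariate. All randomised participants are to be included under intention-to-treat.

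**The concern.** In an individually randomised trial, allocation follows enrolment and so cannot influence who enters. Here enrolment follows allocation and is carried out by people who know the arm. Randomisation balances the practices in expectation, but not the patients those practices go on to recruit.

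Selection can enter at two points. The first is identification: a physician who can offer supervised sessions may think of different patients from one who can offer a brochure, and one inclusion criterion rests on medical judgement. The second is acceptance: patients who agree to a programme of appointments may differ in readiness to change, disease or available time from those who agree to a brochure and postal questionnaires. Both primary outcomes, self-reported activity and PAHCO, are plausibly related to such characteristics. An arm difference could then arise, or a real one be hidden, without any contribution from the intervention. A larger sample would not help, because this is bias and not imprecision. The results are meant to inform national scaling-up, so a recruitment artefact read as an effect would matter.

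**Working it through.** **Step 1: order of events.**

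| Step | Who acts | Arm known to them? |
|---|---|---|
| Practice consents | Physician | No |
| Practice allocated | Research team | n/a |
| Arm-specific training | Physicians and staff | Yes |
| Patients identified | Physicians or staff | Yes |
| Screening and conversation | Physician | Yes |
| Decision to take part | Patient | Informed of own arm's intervention only |
| Baseline measurement (after the advice, per Outcome measures) | Patient | As above |

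The article describes no listing of patients before allocation, no recruiter unaware of the arm, no consecutive-invitation rule and no log of decliners by arm. Identification in advance most naturally means before the appointment; nothing places it before allocation.

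**Step 2: reproduce the planned sample size, to fix the precision.** Inputs from Sample size: f = 0.175, which is d = 0.35 for two groups; α = 0.0125 (two-sided assumed); power 80%; ICC 0.02; 24 practices (1:1 assumed); 10% dropout; N = 567.

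- Per arm, unclustered: 2 × (2.498 + 0.842)² / 0.35² = 182.1, so 183, or 366 in total.
- Analysed: 567 × 0.90 = 510.3, or 21.26 per practice.
- Design effect: 1 + (21.26 − 1) × 0.02 = 1.405.
- 366 × 1.405 = 514. Dividing by 0.90 gives 571; multiplying by 1.10 gives 566. Both are within 3% of 567, so the plan's figure reproduces and is not in dispute.

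**Step 3: precision of the contrast.** SE = √(4 × 1.405 / 510.3) = 0.105 SD, with no allowance for precision gained from baseline adjustment.

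**Step 4: effect of a residual selection difference b.** The b values are assumptions; the protocol gives none. The two-sided test uses noncentral t with 24 − 2 = 22 df, critical value 2.720 and noncentrality b / 0.105.

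| b (SD) | Share of 0.35 | Noncentrality | False-positive rate per test |
|---|---|---|---|
| 0 | 0% | 0 | 1.25% |
| 0.05 | 14% | 0.48 | 2.2% |
| 0.10 | 29% | 0.95 | 5.4% |
| 0.15 | 43% | 1.43 | 12.2% |
| 0.20 | 57% | 1.91 | 23.4% |

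A normal approximation gives slightly higher rates (2.3%, 6.2%, 14.3% and 27.7% for the four non-zero values).

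**Step 5: how much adjustment for the outcome's baseline would remove.** Assume that the arms differ by 0.3 SD in motivation, that motivation correlates 0.4 with the outcome, and that the baseline outcome correlates 0.5 with the follow-up outcome. Let r be the correlation of motivation with the baseline outcome. Residual bias = 0.3 × (0.4 − 0.5r):

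- r = 0: 0.3 × 0.40 = 0.120 SD
- r = 0.3: 0.3 × 0.25 = 0.075 SD
- r = 0.5: 0.3 × 0.15 = 0.045 SD

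Under these assumptions, adjustment shrinks the bias to the extent that the baseline outcome reflects motivation, but does not eliminate it.

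**The case against.** The plan has more protection than its recruitment sequence suggests. Both arms share the eligibility criteria, the 150 min/week inactivity cut-off and the screening assessment. Practices are blocked by area. The brief advice is described as similar in both arms. Patients do not meet the other arm. The planned Reach evaluation and the commitment to CONSORT with its cluster and pragmatic extensions should bring some recruitment data to light. All of this stands, and it narrows differences in eligibility and in reactions to the allocation. None of it controls who is approached or who accepts. Intention-to-treat does not help either: because practices are randomised, analysing every recruited patient carries any selection into the comparison.

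Three stronger readings are tempting but unsupported:

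- A reader might infer that the model adjusts for the outcome's own baseline value and nothing else. Data analysis says only baseline values, and a fuller covariate list may sit in an analysis plan that is not shown.
- A reader might infer that the physician's conversation is about the arm's offer. The text says it concerns the benefits of activity. That patients know the offer when they decide is a reasonable inference from the study information and the rule on what they are told, but it is not stated.
- A reader might infer that the trial will be biased, or biased towards PARS. The protocol supports neither a size nor a direction; every bias value in the tables is assumed.

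The remedies also have limits. Listing patients from records may be harder than it sounds: Participant characteristics reports that some clinical data, such as HbA1c, cannot be retrieved systematically from all practitioners. A fixed invitation rule also fits less easily with recruitment at routine appointments.

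**Conclusion.** The concern holds as a design weakness. Recruitment after allocation by unblinded, arm-trained staff follows from the protocol's own sequence, and no later analysis plan can undo it. The shared criteria, the activity screen and baseline adjustment mitigate the risk but do not close it. Size and direction are unknown. If a residual difference of 0.10 SD remained, the per-test error would be about 5% against a nominal 1.25%; over the assumed range of 0.05 to 0.20 SD it would run from about 2% to 23%. These figures rest on the plan's own ICC, dropout and sample size, a two-sided test, equal allocation, 22 df and no precision gain from covariates. They show what a bias would do, not that one of that size is likely.

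**What to change.** 1. **Practices not yet allocated.** Before a practice learns its arm, have it list potentially eligible patients from its records by diagnosis, age and insurer, and invite from that list by the same rule in both arms. Cost: a short delay and a record query whose feasibility must be confirmed with the practices. Activity level cannot be pre-listed and is still screened at the visit. This limits selective identification but not selective acceptance. Trial status is recruiting, so it is no longer available for practices already allocated.
2. **All practices.** Log invited, ineligible and declining patients by arm, and compare the recruited patients' baseline characteristics between arms. Cost: a simple form per practice. It makes selection visible but does not correct it.
3. **Primary model.** State that, besides the outcome's baseline value, the model adjusts for age, gender, disease type and education, all already collected under Participant characteristics. Add a sensitivity analysis with baseline stage of change and self-efficacy (Secondary outcomes), which come closer to readiness to change. Keep these two out of the primary model because baseline is taken after the advice of a physician who knows the arm, so they could already be affected by it. Cost: a few sentences and no new data.
4. **Reporting.** Acknowledge in the conclusions that residual recruitment bias cannot be excluded.
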